### Intervention

#### BroHealth

BroHealth is an e-mental health program which was developed to reduce men’s risk of having MDE and to improve productivity. The program was designed to be used by working men who don’t have MDE, but are at high risk determined by a multivariable risk prediction algorithm [13]. The development of BroHealth was informed by the results of a national survey in the target population, about high risk men’s preferences for the design features of e-mental health programs [12]. The product was developed at the Digital Emergency Medicine of the University of British Columbia, guided by a committee consisting of research team members with expertise in psychiatry, epidemiology, e-health, occupational psychology, addiction, information technology, and software programming. Before finalization, BroHealth was pilot tested among remaining team members, Stakeholder Advisory Committee members, and the general public recruited through personal networks and social media.

BroHealth contains the following key modules: (1) Information, (2) Self-Help, (3) Self-Check, and (4) Goal Setting and Tracking. The contents of each module are described in Textbox 1.

The contents of each BroHealth module.
Module and content1. Information: information about stress, depression, depression in the workplace, and alcohol use in the workplace.2. Self-Help: a cognitive behavior therapy (CBT) program (Living Life to the Full) developed in the United Kingdom, a mindfulness relaxation program, and specific strategies for dealing with work related issues.3. Self-Check: online instruments for monitoring current depressive and anxiety symptoms, occupational functioning, and future risk of major depression (MDE).4. Goal Setting: the S.M.A.R.T goal setting and tracking system.

BroHealth is a Web-based program that is, at the current stage, opened to research participants only. Participants can log in to BroHealth with a user name and password generated at the Digital Emergency Medicine of University of British Columbia. The novelty of BroHealth is that it was designed in a modular format by which users may select any module/section, without particular sequence. Based on the preferences of the target population and feedback from stakeholders, the contents of the program are balanced with text description and video clips. Moreover, BroHealth has both English and French versions.

#### Telephone-Based Job Coaching

The rationale of including job coaching as part of the intervention is two-fold. First, previous research and our national survey of high-risk working men identified that a limitation of e-mental health programs is the lack of personal interaction [11,12,14]. Second, many RCTs on e-mental health programs suffered from high attrition rates [11,14,15], which is a major threat to the validity of the trials. One contributing factor that emerged from qualitative interviews is that e-mental health programs do not address issues that are relevant to the participants. Therefore, we proposed a combination of BroHealth and job coaching as an intervention arm.

The aim of coaching service is to help users set goals and discover answers to problems for themselves and to motivate users to take actions and engage their own solutions. Coaching is carried out by qualified people who work with clients to improve their effectiveness and performance. Job coaches are individuals who specialize in assisting individuals to learn and accurately carry out job duties. Job coaches provide one-on-one training tailored to the needs of the employee. The coach is well educated, skilled, and experienced in dealing with Human Resources advising, career counseling, goal setting, solution-based problem solving, and performance coaching. In the proposed trial, 5 coaches from different regions of Canada will be hired. Trial participants may access the coaching services in their region through an appointment booking system which is embedded in BroHealth. The coaches in Ontario, Quebec, and Atlantic Canada are bilingual (English and French). Participants will be eligible for one session per week. Each coaching session may last a maximum of 40 minutes.

### Outcomes and Measurements

#### Primary Outcome

The primary outcome is the 12-month risk proportion of MDE, which is the WHO’s Composite International Diagnostic Interview-Short Form (CIDI-SF) [16], will be administered to determine MDE in the past 12 months, based on the Diagnostic and Statistical Manual of Mental Disorders (DSM) criteria [17]. The Composite International Diagnostic Interview-Short Form for Major Depression (CIDI-SFMD) is a structured diagnostic interview for MDE, which has been repeatedly incorporated, without modification, into a series of national health surveys by Statistics Canada, starting in 1994. The CIDI-SFMD was developed from the full version of CIDI to provide a quick screen of MDE [16]. The WHO’s CIDI has been widely used in population-based mental health surveys in different countries. MDE represents a purported 90% predictive cut point for the CIDI-SFMD. Using the full CIDI diagnosis as “gold standard”, the sensitivity and specificity of the CIDI-SFMD was 89.6% and 93.9%, respectively [16].

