**Methods:**

The target population is Canadian working men who are at high risk of having MDE (N=1200). Participants will be recruited using the method of random digit dialing across the country and workplace advertisement. Eligible participants will be randomly allocated into the following groups: (1) a control group, (2) a group receiving BroHealth only, and (3) a group receiving BroHealth and telephone-based job coaching service. The groups will be assessed at 6 and 12 months after randomization. The primary outcome is the risk proportion of MDE over 12 months, which will be assessed by the World Health Organization's (WHO’s) Composite International Diagnostic Interview-Short Form for Major Depression. Intention-to-treat principle will be used in the analysis. The 12-month proportions of MDE in the groups will be estimated and compared. Logistic regression modeling will be used to examine the effect of the intervention on the outcome, controlling for the effects of baseline confounders.

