### Study Setting and Inclusion Criteria

Eligible participants will be recruited from 10 provinces of Canada. Recruitment and fully structured baseline interviews will be conducted by Leger, a Canadian-owned polling and research firm; follow-up interviews will be conducted at the telephone interview laboratory of the Mathison Centre for Mental Health and Education, University of Calgary. The proposed trial will target Canadian male workers who are aged 18 years or older, are working for pay at the time of recruitment, and at the time of recruitment and baseline assessment, are not experiencing a MDE, but have a high risk of having MDE based on our prediction algorithm. Since it was found that 20% of Canadian adult men had a probability of 6.51% or higher in terms of the predicted MDE risk [13], for the proposed study, a personalized risk (or probability) of 6.51% or higher will be defined as high risk for men. In addition, the trial will target workers who may have had MDE in the past 12 months, but are in remission for at least 2 months prior to the study, have no language barriers to English or French, have access to the Internet for personal use, and can provide email and mailing addresses.

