### Randomization

Participants who complete the baseline telephone and online surveys will be randomized into intervention and control groups. The randomization will be conducted and managed by the project coordinator affiliated with the project. To accomplish this, 1200 random numbers (between 0 and 1) will first be generated using Excel (“RAND()”) for 1200 study identification (ID) numbers, ranging from 1 to 1200. The 1200 random numbers will then be sorted in descending order and categorized into 3 equal groups with the ID numbers in the first group (n=400) allocated to the control group, the ID numbers in the second group (n=400) allocated to BroHealth only, and the ID numbers in the third group (n=400) allocated to BroHealth plus job coaching.

The Excel sheet with ID numbers and random numbers will be kept and printed out for randomization. For example, if a participant is the 3rd one to complete the online survey, determined by the date of completion, the project coordinator will search for ID #3 on the Excel sheet. If the random number associated with ID #3 is allocated to the second group, this participant will be assigned to the group that will receive BroHealth only.

The date of randomization will be documented. Any outcomes and/or changes that occur after the randomization will be counted to the groups, regardless of course of the BroHealth and job coaching interventions and if the interventions are used by the participants.

After randomization, the project coordinator will contact the participant by email. For those in the control group, the email will include a link to the men’s mental health page of the Movember Foundation website. For those in the BroHealth only group, the email will include all information to the controls, a link to BroHealth log-in page, and the user name and password, whereas for those in the BroHealth plus job coaching group, the email will include all information to the participants in other groups, and instruction to the coaching appointment booking system in BroHealth.

Afterwards, a package including a thank you letter, the Movember Foundation website link to men’s mental health, and Can $20 incentive as appreciation of their participation will be mailed to the participants.

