### Follow-Up Assessments

The post-randomization assessments will be conducted at 6 and 12 months. At the 6- and 12-month assessments, information regarding demographic and occupational characteristics questions, including changes in marital status and employment, alcohol use, self-rated physical health, CIDI-SFMD, PHQ-9 for depression, GAD-7 for anxiety, WHO’s HPQ, sleep disturbance, anger, quality of life, and mental health service will be collected.

It is anticipated that time is needed to schedule follow-up interviews and there will be conflicts with scheduled interviews (eg, some participants may have to cancel a scheduled interview, or some do not respond to a scheduled phone call). Therefore, a 2-month interview window will be allowed for each follow-up interview.

To obtain in-depth information about how BroHealth affects men’s behaviors and risk profile, qualitative interviews will be conducted via telephone with 10% of the participants in the intervention groups at the end of the RCT (ie, after the 12-month assessment). The participants will represent those with diverse outcomes (clinical and occupational trajectories, and employment status changes). Qualitative interview data will yield in-depth data about the impacts of receiving BroHealth and job coaching on the outcomes. These data will be used to support and interpret the primary quantitative data base. The multiple forms of evidence generated through mixed methods designs are particularly useful for illuminating complex health issues [26].

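### The past-12-month CIDI-SFMD, repeated at 6 months in men who may have had MDE before entry, can re-record old episodes; the plan should say which interviews supply the primary outcome and date onset

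*Protocol article*

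**What the plan says.** All references are to the protocol article.

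- **Outcome.** The abstract (Methods) states: "The primary outcome is the risk proportion of MDE over 12 months". Under Primary Outcome, the CIDI-SF "will be administered to determine MDE in the past 12 months". The same section describes the short form as one "which has been repeatedly incorporated, without modification, into a series of national health surveys".
- **Timing.** Under Follow-Up Assessments: "The post-randomization assessments will be conducted at 6 and 12 months". The list of measures for both interviews includes "self-rated physical health, CIDI-SFMD, PHQ-9 for depression, GAD-7 for anxiety". The section adds that "a 2-month interview window will be allowed for each follow-up interview", without saying whether the window runs before the due date, after it, or both.
- **Eligibility.** Study Setting and Inclusion Criteria admits "workers who may have had MDE in the past 12 months, but are in remission for at least 2 months prior to the study". Recruitment and Screening applies this by excluding men with past-year MDE only if they answer no to the remission question.
- **Intent.** Limitations calls the measured quantity the incidence of MDE. Sample Size Calculation takes its rates, 0.8% and 3.9%, from trial participants who developed MDE over 12 months. Randomization says: "Any outcomes and/or changes that occur after the randomization will be counted to the groups".

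The article mentions no shorter recall period at 6 months and no question on date of onset. It gives no rule for setting aside an episode already recorded at screening, and does not say whether one or both interviews supply the primary outcome.

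**The concern.** The recall period is as long as the whole follow-up but is first applied halfway through it. A man who screened positive for a past-year episode, and entered because he had been well for two months, can report the same episode at month 6 and be scored positive again. No intervention given after randomisation could have prevented that event.

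The trial is about prevention and its planned event rates are very low, so a few such positives per arm matter. One of the inputs to the entry risk algorithm is personal history of MDE (Recruitment and Screening), so men with recent episodes are unlikely to be absent from the sample. The point also has a deadline: if the interview does not collect onset dates, no later analysis plan can recover them.

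**Working it through.** **Step 1: what each interview covers.** Months are counted from randomisation, and recall is 12 months. The remission rule keeps roughly months −2 to 0 free of MDE, ignoring any gap between screening and randomisation.

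| Interview held at | Recall covers | Pre-entry time where an episode is possible | Follow-up missed or added |
|---|---|---|---|
| 6 | −6 to 6 | −6 to −2 | none |
| 8 (late, if window runs forward) | −4 to 8 | −4 to −2 | none |
| 10 (12-month visit, if window runs backward) | −2 to 10 | essentially none | 10 to 12 not yet observed |
| 12 | 0 to 12 | none | none |
| 14 (late, if window runs forward) | 2 to 14 | none | 0 to 2 missed, 12 to 14 added |

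Carry-over therefore arises at the 6-month interview. It reaches the primary outcome only if that interview contributes to it.

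**Step 2: reproduce the plan's sample size.** Inputs from Sample Size Calculation: p₁ = 0.008, p₂ = 0.039, power 0.80, alpha 0.05 (taken as two-sided). With p̄ = 0.0235 and the usual formula without continuity correction:

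n = [1.960·√(2p̄(1−p̄)) + 0.842·√(p₁(1−p₁) + p₂(1−p₂))]² / (p₂−p₁)²

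= [1.960 × 0.2142 + 0.842 × 0.2131]² / 0.031² = 0.3591 / 0.000961 ≈ 373.7, so 374 per arm.

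This matches the plan. At the 400 per arm to be recruited, power is 0.83 before any attrition.

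**Step 3: add carried-over positives.** Let q be the share of men in each arm who are scored positive only because of a pre-randomisation episode. The article gives no figure for q, so it is an assumption shown as a range. The rates become p* = q + (1−q)p. For q = 1%:

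- intervention: 0.01 + 0.99 × 0.008 = 0.0179
- control: 0.01 + 0.99 × 0.039 = 0.0486

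| q (assumed) | Intervention | Control | Relative risk | Power at 374 | Power at 400 | n per arm for 0.80 |
|---|---|---|---|---|---|---|
| 0 | 0.8% | 3.9% | 0.21 | 0.80 | 0.83 | 374 |
| 0.5% | 1.3% | 4.4% | 0.30 | 0.72 | 0.75 | 454 |
| 1% | 1.8% | 4.9% | 0.37 | 0.65 | 0.68 | 535 |
| 2% | 2.8% | 5.8% | 0.48 | 0.54 | 0.56 | 700 |
| 5% | 5.8% | 8.7% | 0.66 | 0.34 | 0.36 | 1214 |

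The risk difference shrinks only by the factor (1−q), from 3.10 to 3.07 percentage points at q = 1%. Most of the power loss comes from the larger variance once non-preventable events are added to such low rates. At q = 1% that is 4 men per arm of 400, against 400 × 0.008 = 3.2 expected events in an intervention arm.

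The calculation assumes that carried-over positives are equally common in each arm and that those men otherwise have the average risk of a new episode. Here q counts only men who actually report the old episode and are scored on it, so it is smaller than the share who had one.

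**The case against.** The strongest reply is that nothing in the article makes the 6-month interview part of the primary outcome. A 12-month risk measured with a 12-month instrument points naturally to the 12-month interview, where recall and follow-up coincide. Even if that interview came two months early, the recall would reach back only into the required remission period. On this reading q is about zero and no power is lost. This objection stands, and it is why the point is conditional. It does not remove the point: the article does not state this reading, and it gives the CIDI-SFMD at both visits.

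A reader might infer that the plan contradicts itself, because the Randomization section counts post-randomisation outcomes. The text does not support that. The sentence is an intention-to-treat statement about assigning outcomes to groups whether or not the interventions are used. It does not say that only such outcomes count, and it gives no way of dating an episode. If anything, it shows the right intent.

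It can also be said that interview wording and event derivation belong in the full protocol or the interview script. That is fair, and the script may already handle this. The remark about unmodified use concerns the national surveys and does not settle what this trial asks at month 6. A later analysis plan alone, however, cannot supply onset dates that were not asked for. Screening identifies men with past-year MDE, so adjustment for that history is possible. It still cannot tell whether a positive result at month 6 is an old or a new episode.

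Finally, randomisation should balance old episodes across arms. That is correct, so a reader should not infer bias in favour of the intervention.

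**Conclusion.** The point holds conditionally. As described, a 6-month interview can re-record an episode from about 2 to 6 months before randomisation, and the article neither states nor excludes that this interview feeds the primary outcome.

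- **If it does,** the outcome partly measures past history. With q assumed between 0.5% and 5%, power at 400 per arm falls from 0.83 to between 0.75 and 0.36, and the expected relative risk moves from 0.21 to between 0.30 and 0.66.
- **If only the 12-month interview counts,** carry-over is essentially nil and power is unaffected. The remaining issue is smaller: if the window runs forward, an interview as late as month 14 misses the first two months after randomisation and adds two beyond month 12.

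It would go too far to say that the plan will count pre-entry episodes, or that q is known to be large; the article supports neither. The sample size of 374 is correct for its stated inputs. This should be fixed before follow-up starts.

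**What to change.** 1. State which interview or interviews supply the primary outcome.
2. Define the primary event as an MDE with onset after the randomisation date and within 12 months of it.
3. Make the interview able to deliver that definition, in one of two ways:
   - ask about the time since randomisation at 6 months, and since the last interview at 12 months (since randomisation for men who missed the 6-month interview); or
   - keep the standard past-12-month wording and add one question on month of onset.

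The onset question also allows events after month 12 to be set aside when an interview runs late. If the standard wording is kept, using both interviews covers the early weeks that a late 12-month interview would miss.

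The cost is a change to the interview script and the endpoint wording: either a small departure from the standard recall period, with some loss of comparability with the national surveys, or one extra question. The planned rates and sample size are unchanged, because they already refer to newly developed MDE.

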#### Secondary Outcomes

Secondary outcome variables are changes in depression and anxiety scores, and absenteeism and presenteeism. Depression will be measured by the 9-item Patient Health Questionnaire (PHQ-9); anxiety will be measured by the 7-item Generalized Anxiety Disorder (GAD-7). The PHQ-9 is a widely used scale for assessing depressive symptoms [18], which scores each of the 9 symptoms from 0 (not at all) to 3 (nearly every day) [18]. A PHQ-9 score of greater than or equal to 10 has a sensitivity of 88% and a specificity of 88% for MDE [18]. The GAD-7 is widely used as a general screen for common symptoms of anxiety. The GAD-7 has good reliability and validity. A cut point was identified that optimizes sensitivity (89%) and specificity (82%) [19].

Absenteeism and presenteeism will be measured by the WHO’s Health Performance Questionnaire (HPQ) [20,21] and the Lam Employment Absence and Productivity Scale (LEAPS) [22]. The HPQ is a brief self-report questionnaire that obtains screening information about the prevalence and treatment of commonly occurring health problems, and information about 3 types of workplace consequences (sickness absence, presenteeism, and critical incidents). LEAPS is a validated scale for measuring occupational functioning for workers with depression.

#### Predicted Risk and Probability of MDE

Predicted risk and/or probability of MDE will be measured using the sex-specific risk prediction algorithm [13]. This risk prediction algorithm is to be used in individuals who do not have MDE. Based on exposure to a key set of risk factors including family history, current health status, childhood trauma, and ongoing life stressors, the algorithm can generate a person’s probability of having MDE in the next 4 years [13]. The algorithm was developed using the data from over 4700 Canadian men who were followed for 4 years [13].

#### Return on Investment

Based on the HPQ, lost work productivity will first be calculated. The financial value of lost work productivity will be calculated as:

Value = (A x B) x C

where A is the absolute hours of combined lost work productivity (from change over time from baseline period to follow-up period in absenteeism hours and poor job performance/presenteeism hours), B is the financial value of hour of employee compensation (wages + benefits value), and C is the economic productivity multiplier (1.25). An example is shown in Textbox 2.

An example of the financial value of lost work productivity equation.
ExamplePer 1 month:37 hours of lost productive time x $50 per hour = $1850$1850 x 1.25 = $2312.50 totalThis can be extrapolated to the entire year:$2312.50 x 12 = $27,750 lost per person per yearHowever, this is a high estimate as normal workers are not 100% productive while at work, nor are they never absent from work. So this can also be adjusted to take into account normative employee levels of lost work time.

### Other Variables

Other variables include demographic and socioeconomic characteristics, occupation, employment status, job gradient, parental and marital strain [23], self-rated physical health, alcohol use, sleep disturbance, anger, quality of life, and mental health service use. Alcohol use will be measured by the 3-item Alcohol Use Disorders Identification Test (AUDIT-C). Sleep disturbance and anger will be assessed using the measures of Patient-Reported Outcome Measurement Information System (PROMIS) of the US Department of Health and Human Services. Quality of life will be assessed by the EuroQol five dimensions questionnaire (EQ-5D) which is a widely used instrument for quality of life [24]. Questions about mental health service use are adopted from Statistics Canada’s national health surveys.

